## Abstract

**Background:**

Primary Sjogren’s syndrome (pSS) is a systemic autoimmune disease involving multiple organ systems. The Janus kinase/signal transduction and activator of transcription (JAK/STAT) signaling pathway is a key pathway involving the pathogenesis of pSS. Baricitinib, a selective JAK1 and JAK2 inhibitor, has been approved for treatment of active rheumatoid arthritis and reported in treatment of some other autoimmune diseases including systemic lupus erythematosus. We have found that baricitinib might be effective and safe in pSS in a pilot study. However, there is no published clinical evidence of baricitinib in pSS. Hence, we conducted this randomized study to further explore the efficacy and safety of baricitinib in pSS.

**Methods:**

This is a multi-center, prospective, open-label, randomized study to compare the efficacy of baricitinib + hydroxychloroquine (HCQ) with HCQ alone in pSS patients. We plan to involve 87 active pSS patients with European League Against Rheumatism pSS disease activity index (ESSDAI) ≥ 5 from eight different tertiary centers in China. Patients will be randomized (2:1) to receive baricitinib 4 mg per day + HCQ 400 mg per day or HCQ 400 mg per day alone. We will switch HCQ to baricitinib + HCQ if the patient in the latter group has no ESSDAI response at week 12. The final evaluation will be at week 24. The primary endpoint is the percentage of ESSDAI response, or minimal clinically important improvement (MCII), which was defined as an improvement of ESSDAI at least three points at week 12. The secondary endpoints include EULAR pSS patient-reported index (ESSPRI) response, change of Physician’s Global Assessment (PGA) score, serological activity parameters, salivary gland function test, and focus score on labial salivary gland biopsy.

**Discussion:**

This is the first randomized controlled study to evaluate the clinical efficacy and safety of baricitinib in pSS. We hope that the result of this study can provide more reliable evidence of the efficacy and safety of baricitinib in pSS.

**Trial registration:**

ClinicalTrials.gov NCT05016297. Registered on 19 Aug 2021.

## Administrative information

Note: the numbers in curly brackets in this protocol refer to SPIRIT checklist item numbers. The order of the items has been modified to group similar items (see http://www.equator-network.org/reporting-guidelines/spirit-2013-statement-defining-standard-protocol-itemsfor-clinical-trials/).

## Introduction

### Background and rationale {6a}

Primary Sjogren’s syndrome (pSS) is a systemic autoimmune disease characterized by dysfunction of the exocrine glands. The clinical hallmarks of pSS are keratoconjunctivitis sicca and xerostomia, or the sicca complex. Important organs including renal, pulmonary, or central nervous system involvement can be seen in patients with pSS. The manifestations of pSS result from a predominantly lymphocytic cell infiltration of glandular and non-glandular organs. The abnormal activation of T helper (Th) 1/Th17 lymphocytes, B lymphocytes, and plasma cells are related to the pathogenesis of pSS.

Th17 cells, as an important subset of CD4 + T cells, have been recognized in recent years. Under the stimulation of interleukin(IL)-6, transforming growth factor(TGF)-β, IL-21, IL-23, and other cytokines, CD4 + T cells can differentiate into Th17 cells, which with highly expression of RoRγt, and secrete IL-17, IL-22 and other cytokines to promote the activation of B-cells and promote the inflammatory response of target organs [1, 2]. Many literatures have found that Th17 cells and its related cytokines such as IL-17 are activated and increased in peripheral blood [3], salivary gland tissue [4], and tear [5] of patients with pSS. In a variety of Sjogren’s syndrome animal models, including C57BL/6.NOD-Aec1Aec2 mice, abnormal activation of Th17 cells, increased IL-17 levels, and infiltration of Th17 cells in salivary gland tissue were found [6]. These studies verified that Th17 cells play an important role in the pathogenesis of pSS.

Janus kinase (JAK) / (signal transducer and activator of transcription) STAT signaling pathway is activated and plays as a key pathway in the differentiation and activation of many lymphocytes, which affect the pathogenesis of many autoimmune diseases [7]. Many studies had identified that JAK/STAT signaling pathway was the key pathway of Th17 cell differentiation and activation. Genome-wide association studies (GWASs) had shown that STAT3 plays a key role in transcriptional regulation during early differentiation of Th17 cells [8]. Several in vitro and animal experiments have revealed that inhibition of JAK/STAT pathway, especially JAK1-3/STAT3 pathway, can inhibit the differentiation and function of Th17 cells in animal models including ankylosing spondylitis [9], psoriasis [10], and autoimmune arthritis [11, 12]. JAK/STAT pathway was also playing a key role in the activation of interferon (IFN), especially type I IFN, which was important in the pathogenesis of many systemic autoimmune diseases [13], such as systemic lupus erythematosus (SLE) and pSS [14]. So JAK/STAT pathway may take part in the process of many autoimmune diseases including pSS by affecting many cytokine signals.

JAK inhibitors have also been widely used in the treatment of rheumatoid arthritis (RA) and other autoimmune diseases [7]. Some studies have verified that JAK/STAT pathway is activated in patients with pSS, and JAK inhibitor may be effective for pSS. Lee et al. found that filgotinib, the selective JAK1 inhibitor, suppressed the IFN-induced transcription of differentially expressed genes and B-cell activating factor (BAFF) in human primary salivary gland epithelial cells [15]. In addition, filgotinib-treated mice exhibited increased salivary flow rates and marked reductions in the lymphocytic infiltration of salivary glands. JAK inhibitors AG490 and ruxolitinib can reverse DNA methylation and hydroxymethylation of salivary gland epidermal cells in pSS [16]. All these basic studies had shown that JAK inhibitors might be a novel therapeutic approach for pSS. A randomized phase 2 study is currently in progress to assess the safety and efficacy of filgotinib in adult subjects with active Sjogren’s syndrome (ClinicalTrials.gov ID: NCT03100942). A phase 1/2 study of JAK inhibitor tofacitinib demonstrated a trend for improving both signs and symptoms of patients with dry eye disease. So far, only one basic study has focused on baricitinib for pSS [17], in which Aota et al. demonstrated baricitinib suppressed IFN-γ induced CXCL10 expression in human salivary gland ductal cells and suggested its potential for the treatment of pSS. There is no evidence of the safety and efficacy of baricitinib in patients with pSS. We plan to conduct this study to explore the efficacy and safety of baricitinib in pSS.

### Objectives {7}

We hope to provide reliable evidence of baricitinib as a new potential oral therapy for pSS. The primary endpoint is the percentage of European League Against Rheumatism (EULAR) pSS disease activity index (ESSDAI) response, or minimal clinically important improvement (MCII), which was defined as an improvement of ESSDAI at least three points [18], at 12 weeks.

### Trial design {8}

This is a multi-center, prospective, open-label, randomized study to compare the efficacy of baricitinib + hydroxychloroquine (HCQ) with HCQ alone in pSS patients. Patients will be randomized (2:1) to receive baricitinib 4 mg per day + HCQ 400 mg per day or HCQ 400 mg per day alone. We will switch HCQ to baricitinib + HCQ if the patient in the latter group has no response at week 12. The final evaluation will be at week 24.

## Methods: participants, interventions, and outcomes

### Study setting {9}

This study will be performed in eight tertiary referral centers (Peking Union Medical College Hospital, et al.) in China. Patients are recruited at the outpatient clinic of department of rheumatology in these hospitals. Patients are considered for inclusion if they meet the criteria as defined below.

### Eligibility criteria {10}

#### Inclusion criteria

Must read and understand the informed consent approved by the institutional review board (IRB)/ethics review board (ERB) governing the site and provide written informed consent.Stated willingness to comply with all study procedures and availability for the duration of the study.Ability to take oral medication and be willing to adhere to the study intervention regimen.Male or female, aged between 18 and 75 years.Fulfill the 2016 ACR/EULAR classification criteria for pSS [19].With moderate activity (ESSDAI ≥ 5) on HCQ 400 mg per day treatment for at least 12 weeks at the screening visit.With serological activity defined as hypocompleminemia or elevated C-reactive protein (CRP)/erythrocyte sedimentation rate (ESR)/immunoglobulin G (IgG) /rheumatoid factor (RF) level (excluding acute and chronic infection and other factors).Nonpregnant, nonbreastfeeding female patient.Males with potential for reproduction must agree to practice effective birth control methods described above too.

#### Exclusion criteria

Have received any of the following medications:aBiologic treatments for immunologic disease such as etanercept, infliximab, certolizumab, adalimumab, golimumab, tocilizumab, abatacept, ustekinumab, ixekizumab, secukinumab, or anakinra within 4 weeks of screening.
Cyclophosphamide (or any other cytotoxic agent), belimumab, or anifrolumab (or another anti-IFN therapy) within 12 weeks of screening.bCyclophosphamide (or any other cytotoxic agent), belimumab, or anifrolumab (or another anti-IFN therapy) within 12 weeks of screening.cRituximab, any other B-cell depleting therapies, or intravenous immunoglobulin (IVIg), or pulse methylprednisolone within 24 weeks of screening.dGlucocorticoids which dosage greater than 10 mg prednisone per day.eMethotrexate, azathioprine, mycophenolate mofetil, cyclosporine, tacrolimus within 4 weeks at the time of screening.fPlasmapheresis within 12 weeks of screening.History of chronic liver disease or elevated liver function tests:a
Alanine aminotransferase (ALT) or aspartate aminotransferase (AST) > 2 × upper limit of normal at screening.bSerum total bilirubin ≥ 1.5 × upper limit of normal at screening.With estimated glomerular filtration rate (eGFR) < 40 mL/min/1.73 m2 (Bedside Schwartz formula 2009) or have received hemodialysis, peritoneal dialysis, or intestinal dialysis.Protein to creatinine ratio of more than 1 mg/dL repeated and confirmed three times or confirmed with 24 h urine protein of more than 1000 mg.White blood cell (WBC) < 2 × 109 cells/L or absolute neutrophil count (ANC) < 1 × 109 cells/L, hemoglobin (Hgb) < 9.0 g/dL or platelets < 1 × 109 cells/L or absolute lymphocyte count (ALC) < 0.5 × 109 cells/L.Have screening laboratory test values, including thyroid-stimulating hormone (TSH), outside the reference range for the population that, in the opinion of the investigator, pose an unacceptable risk for the patient’s participation in the study. Patients who are receiving thyroxine as replacement therapy may participate in the study, provided stable therapy has been administered for ≥ 12 weeks and TSH is within the laboratory’s reference range. Patients who have TSH marginally outside the laboratory’s normal reference range and are receiving stable thyroxine replacement therapy may participate if the treating physician has documented that the thyroxine replacement therapy is adequate for the patient.Pregnant or lactating women. Women of childbearing potential are required to have a negative pregnancy test at screening.Have had any major surgery within 8 weeks prior to screening or will require major surgery during the study that, in the opinion of the investigator, would pose an unacceptable risk to the patient.Have experienced any of the following within 12 weeks of screening: venous thromboembolism (VTE, deep vein thrombosis [DVT] /pulmonary embolism [PE]), myocardial infarction, unstable ischemic heart disease, stroke, New York Heart Association Stage III/IV heart failure, or have a history of recurrent (≥ 2) VTE (DVT/PE).Have a history or presence of cardiovascular, respiratory, hepatic, gastrointestinal, endocrine, hematological, neurological, or neuropsychiatric disorders or any other serious and/or unstable illness that in the opinion of the investigator, could constitute an unacceptable risk when taking investigational product or interfere with the interpretation of data.Have a history of lymphoproliferative disease; have signs or symptoms suggestive of possible lymphoproliferative disease, including lymphadenopathy or splenomegaly; have active primary or recurrent malignant disease; or have been in remission from clinically significant malignancy for < 5 years prior to randomization. The following may be exempted:a
Patients with cervical carcinoma in situ that has been resected with no evidence of recurrence or metastatic disease for at least 3 years may participate in the study.bPatients with basal cell or squamous epithelial skin cancers that have been completely resected with no evidence of recurrence for at least 3 years may participate in the study.Have a current or recent (< 4 weeks prior to randomization) clinically serious viral, bacterial, fungal, or parasitic infection or any other active or recent infection that in the opinion of the investigator, would pose an unacceptable risk to the patient if participating in the study.Have symptomatic herpes simplex at the time of randomization, a history of disseminated/complicated herpes zoster, or have had symptomatic herpes zoster infection within 12 weeks prior to randomization.Have a positive test for hepatitis B virus (HBV) defined as:aPositive for hepatitis B surface antigen (HBsAg), orbPositive for hepatitis B core antibody (HBcAb) and positive for hepatitis B virus deoxyribonucleic acid (HBV DNA). Note: Patients who are HBcAb-positive and HBV DNA-negative may be enrolled in the study but will require additional HBV DNA monitoring during the study.Have hepatitis C virus (HCV) infection (hepatitis C antibody-positive and HCV ribonucleic acid [RNA]-positive). Note: Patients who have documented anti-HCV treatment for a past HCV infection AND are HCV RNA-negative may be enrolled in the study.Have evidence of human immunodeficiency virus (HIV) infection and/or positive HIV antibodies.Have had household contact with a person with active tuberculosis (TB) and did not receive appropriate and documented prophylaxis for TB.Have evidence of active TB or latent TB.aHave evidence of active TB, defined in this study as the following: Positive purified protein derivative (PPD) test (≥ 5 mm induration between approximately 2 and 3 days after application, regardless of vaccination history), medical history, clinical features, and abnormal chest X-ray at screening. QuantiFERON®-TB Gold test or T-SPOT®.TB test (as available and if compliant with local TB guidelines) may be used instead of the PPD test. Patients are excluded from the study if the test is not negative and there is clinical evidence of active TB. Exception: patients with a history of active TB who have documented evidence of appropriate treatment, have no history of re-exposure since their treatment was completed, have no clinical features of active TB, and have a screening chest X-ray with no evidence of active TB may be enrolled if other entry criteria are met. Such patients would not be required to undergo the protocol-specific TB testing for PPD, QuantiFERON®-TB Gold test, or T-SPOT®.TB test but must have a chest X-ray at screening (i.e., chest imaging performed within the past 6 months will not be accepted).bHave evidence of untreated/inadequately or inappropriately treated latent TB, defined in this study as the following: Positive PPD test, no clinical features consistent with active TB, and a chest X-ray with no evidence of active TB at screening; or If the PPD test is positive and the patient has no medical history or chest X-ray findings consistent with active TB, the patient may have a QuantiFERON®-TB Gold test or T-SPOT®.TB test (as available and if compliant with local TB guidelines). If the test results are not negative, the patient will be considered to have latent TB (for purposes of this study); or QuantiFERON®-TB Gold test or T- SPOT®.TB test (as available and if compliant with local TB guidelines) may be used instead of the PPD test. If the test results are positive, the patient will be considered to have latent TB. If the test is not negative, the test may be repeated once within approximately 2 weeks of the initial value. If the repeat test results are again not negative, the patient will be considered to have latent TB (for purposes of this study). Exception: Patients who have evidence of latent TB may be enrolled if he or she completes at least 4 weeks of appropriate treatment prior to randomization and agrees to complete the remainder of treatment while in the trial. Exception: Patients with a history of latent TB who have documented evidence of appropriate treatment, have no history of re-exposure since their treatment was completed, have no clinical features of active TB, and have a screening chest X-ray with no evidence of active TB may be enrolled if other entry criteria met. Such patients would not be required to undergo the protocol-specific TB testing for PPD, QuantiFERON®-TB Gold test, or T-SPOT®.TB test but must have a chest X-ray at screening (i.e., chest imaging performed within the past 6 months will not be accepted).Have been exposed to a live vaccine within 12 weeks of randomization or are expected to need/receive a live vaccine during the study (except for herpes zoster vaccination).Are currently enrolled in or have discontinued within 4 weeks of screening from any other clinical trial involving an investigational product or nonapproved use of a drug or device or any other type of medical research judged not to be scientifically or medically compatible with this study.Participants with active renal or central nervous system disease or significant impairment of major organ function (lung, heart, liver, kidney) or any condition that, in the opinion of the Investigator, would jeopardize the participant’s safety following exposure to the study drug.Psychiatric illness or history of medical non-compliance that the study team feels will make the patient unlikely to complete the study.Known allergic reactions to baricitinib or its components.Are largely or wholly incapacitated permitting little or no self-care, such as being bedridden or confined to wheelchair.In the opinion of the investigator, are at an unacceptable risk for participating in the study.Have donated more than a single unit of blood within 4 weeks prior to screening or intend to donate blood during the study.Have a history of intravenous drug abuse, other illicit drug abuse, or chronic alcohol abuse within the 2 years prior to screening or are concurrently using, or expected to use during the study, illicit drugs (including marijuana).Are unable or unwilling to make themselves available for the duration of the study and/or are unwilling to follow study restrictions/procedures.

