### Criteria for discontinuing or modifying allocated interventions {11b}

#### Temporary interruption of investigational product

In some circumstances, patients may need to temporarily interrupt treatment as a result of abnormal laboratory values that may have an unclear relationship to investigational product.

For the abnormal laboratory findings and clinical events (regardless of relatedness) listed in Table 1, specific guidance is provided for temporarily interrupting treatment and when treatment may be restarted. Retest frequency and timing of follow-up laboratory tests to monitor the abnormal finding is at the discretion of the investigator. Investigational product that was temporarily interrupted because of an adverse event or abnormal laboratory value not specifically covered in Table 1 may be restarted at the discretion of the investigator.

**Table 1 Tab1:** Temporary interruption due to some abnormal laboratory values

Laboratory measure	Action	Monitoring guidance
Absolute neutrophil count (ANC)	Treatment should be interrupted if ANC < 1 × 10^9^ cells/L and may be restarted once ANC return above this value	Before treatment initiation (see exclusion criteria too) and thereafter according to routine patient management
Absolute lymphocyte count (ALC)	Treatment should be interrupted if ALC < 0.5 × 10^9^ cells/L and may be restarted once ALC return above this value	
Hemoglobin (Hgb)	Treatment should be interrupted if Hgb < 8 g/dL and may be restarted once Hgb return above this value	
Hepatic transaminases	Treatment should be temporarily interrupted if drug-induced liver injury is suspected	

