### Permanent discontinuation from investigational product

Investigational product must be permanently discontinued if the patient or the patient’s designee requests to discontinue investigational product.

Discontinuation of the investigational product for abnormal liver tests should be considered by the investigator when a patient meets 1 of the following conditions:ALT or AST > 8 × upper limit of normalALT or AST > 5 × upper limit of normal for more than 2 weeks after temporary interruption of investigational productALT or AST > 3 × upper limit of normal and total bilirubin level > 2 × upper limit of normalALT or AST > 3 × upper limit of normal with the appearance of fatigue, nausea, vomiting, right upper quadrant pain or tenderness, fever, rash, and/or eosinophilia (> 5%)

Investigational product should be permanently discontinued if any of the following laboratory abnormalities are observed:WBC < 1 × 10^9^ cells/LANC < 0.5 × 10^9^ cells/LALC < 0.2 × 10^9^ cells/LHgb < 6.5 g/dL

Temporary interruption rules must be followed where applicable. For laboratory values that meet permanent discontinuation thresholds, investigational product should be discontinued. However, if in the opinion of the investigator the laboratory abnormality is due to intercurrent illness such as cholelithiasis or another identified factor, laboratory tests may be repeated. Only when the laboratory value meets resumption thresholds (Table 1) following the resolution of the intercurrent illness or other identified factors may the investigator restart investigational product.

In addition, patients will be discontinued from investigational product in the following circumstances:PregnancyMalignancyDevelopment of a VTE (DVT/PE) during the study

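### The platelet exclusion limit of 1 × 10^9/L cannot be a working clinical threshold, and the article gives no other platelet number

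*Protocol article*

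**What the plan says.** The hematology criterion under Exclusion criteria in the protocol article sets limits for white cells (2), neutrophils (1), hemoglobin, platelets and lymphocytes (0.5). The platelet part reads "hemoglobin (Hgb) < 9.0 g/dL or platelets < 1 × 109 cells/L". All four cell counts in that criterion carry the same multiplier, shown as 109 because the superscript was lost.

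Four further exclusions could catch a low platelet count, all of them by judgement:

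- screening laboratory values "outside the reference range for the population that, in the opinion of the investigator, pose an unacceptable risk";
- "hematological, neurological, or neuropsychiatric disorders or any other serious and/or unstable illness that in the opinion of the investigator, could constitute an unacceptable risk";
- "significant impairment of major organ function (lung, heart, liver, kidney) or any condition that, in the opinion of the Investigator, would jeopardize the" participant's safety;
- the general clause "In the opinion of the investigator, are at an unacceptable risk for participating in the study".

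On treatment, Table 1 (Temporary interruption of investigational product) has rows for neutrophils, lymphocytes, hemoglobin and transaminases. The neutrophil row, for example, reads "Treatment should be interrupted if ANC < 1 × 10^9^ cells/L and may be restarted once ANC return above this value". After an interruption for any other reason, treatment stopped for an adverse event or an "abnormal laboratory value not specifically covered in Table 1 may be restarted at the discretion of the investigator". The section on permanent discontinuation states "Investigational product should be permanently discontinued if any of the following laboratory abnormalities are observed" and then lists white cells, neutrophils, lymphocytes and hemoglobin. Neither place mentions platelets.

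Table 2 (Participant timeline) schedules a complete blood count at every visit. Trial status says that screening began on February 12th, 2022 under protocol version 3.1.

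**The concern.** A platelet limit with the same numerical value as a neutrophil limit is implausible, because the two counts lie on very different scales. As printed, the rule would let a patient with severe thrombocytopenia pass the platelet criterion. The Discussion names hematological involvement among the manifestations seen in the pilot study, so low counts are foreseeable in this population.

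If the error is confined to the article, readers and anyone reusing the criteria are given a false safety threshold. If protocol version 3.1 and the eCRF carry the same figure, the numeric screen does nothing at any of the eight centers. A monitor checking eligibility in the planned 25% sample would also find such a patient compliant with this criterion. The trial has no data safety monitoring board and no interim safety analysis to act as a further check.

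**Working it through.** **1. Is the figure an artefact of lost superscripts?** Two of the four counts recur in Table 1, where the superscript is marked:

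| Count | Exclusion criteria | Table 1 |
|---|---|---|
| Neutrophils | 1 × 109 | 1 × 10^9 |
| Lymphocytes | 0.5 × 109 | 0.5 × 10^9 |

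So 109 means 10^9 throughout the criterion. The white-cell, neutrophil and lymphocyte limits are plausible on that reading; only the platelet multiplier is not. The error lies in the 1, not in the exponent's formatting.

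**2. Size of the limit.** 1 × 10^9/L ÷ 10^6 = 1,000 per microlitre. Within the criterion, platelets/neutrophils = 1/1 = 1.0 and platelets/white cells = 1/2 = 0.5.

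**3. Against what may have been intended.** The article gives no intended value, so I assume a wide range:

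| Assumed limit (× 10^9/L) | Printed ÷ assumed |
|---|---|
| 20 | 1/20 = 5% |
| 50 | 1/50 = 2% |
| 100 | 1/100 = 1% |
| 150 | 1/150 = 0.7% |

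**4. Whom would it exclude?** This is an illustration only, with assumed log-normal counts: share below t = Φ(ln(t/median)/log-SD).

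| Median (× 10^9/L), log-SD | Below 1 (printed) | Below 50 | Below 100 |
|---|---|---|---|
| 230, 0.3 | about 0 | about 0% | 0.3% |
| 150, 0.5 | about 0 | 1.4% | 21% |
| 80, 0.6 | 1.4 × 10^-13 | 22% | 65% |

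Even in a population with a median of 80, the printed limit excludes practically nobody, whereas a limit of 50 or 100 would exclude a material share.

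**5. Is there another numeric platelet limit?** On-treatment limits, from Table 1 and the permanent discontinuation list:

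| Parameter | Interrupt | Discontinue | Number of limits |
|---|---|---|---|
| White cells (× 10^9/L) | none | 1 | 1 |
| Neutrophils (× 10^9/L) | 1 | 0.5 | 2 |
| Lymphocytes (× 10^9/L) | 0.5 | 0.2 | 2 |
| Hemoglobin (g/dL) | 8 | 6.5 | 2 |
| Platelets | none | none | 0 |

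The total is 1 + 2 + 2 + 2 = 7 for the other four parameters and 0 for platelets. The entry figure is the only platelet number in the article.

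**6. What would detect a low count?** A blood count is taken at screening and at weeks 0, 4, 8, 12, 16, 20 and 24, which is 8 of 8 visits. The count would be seen; what is missing is a valid number to compare it with.

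**7. Two minor slips in the same list.** The eGFR limit names the Bedside Schwartz formula, which is a pediatric equation, while the trial enrols ages 18 to 75. That it is pediatric is general knowledge, not stated in the article. The protein-to-creatinine ratio is given in mg/dL, a concentration unit that a ratio cannot carry. Assuming 800, 1000 or 1500 mg creatinine excreted per day, a ratio of 1 mg/mg gives 1 × 800 = 800, 1 × 1000 = 1000 or 1 × 1500 = 1500 mg protein per 24 h. This is in line with the article's alternative of 1000 mg.

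**The case against.** The strongest reply is that this is probably a transcription error in a journal article with little practical consequence. Protocol version 3.1 and the eCRF are not shown and may carry the right value. If they do not, an investigator would still see a very low count at screening and could exclude the patient under any of four clauses, two of which address laboratory values and hematological disorders directly. On treatment, the article foresees interruptions for laboratory abnormalities outside Table 1, treats abnormal blood tests as adverse events, and lets the investigator decide whether a patient leaves the study because of one. The lack of an on-treatment platelet limit is not a false statement either: an article may leave such limits to the full protocol.

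Most of this stands as to weight. Admission of a patient at real risk is unlikely, and the tally of on-treatment limits serves only to show that no other platelet number can stand in for the wrong one. The reply does not rescue the figure. The complaint is not that a limit was left to another document; a limit is stated, and it is wrong as stated. Discretion was meant to supplement the numeric rule, not to replace it.

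The two minor points carry little weight. The 24 h protein limit still works, and the exclusion for active renal disease or organ impairment is a backstop for the eGFR rule.

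**Conclusion.** The concern holds. The platelet exclusion limit is wrong as written. It is 0.7% to 5% of any assumed limit between 150 and 20 × 10^9/L, it excludes practically nobody, and no other numeric platelet limit exists in the article at entry or on treatment. The intended limits and the count distributions are assumptions; the conclusion is insensitive to them.

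The intended value cannot be recovered from the article, and whether version 3.1 and the eCRF share the error is unknown. The consequence is confined to the safety screen and to what readers are told. There is no effect on the primary endpoint, the sample size or the analysis. The point does not depend on the eGFR formula or the ratio unit.

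**What to change.** - Check the platelet limit against protocol version 3.1 and the eCRF, and replace it with the clinically intended value. The sponsor has to set this value, since the article does not give it.
- If only the article is wrong, publish an erratum.
- If the protocol carries the same figure, make a minor amendment, update the eCRF edit check, and re-check the screening platelet counts already collected.
- In the same correction, name an eGFR equation for adults. Also check the protein-to-creatinine unit against the full protocol and state the limit as a true ratio; 1 mg/mg (1 g/g) would agree with 1000 mg per 24 h.

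The cost is low. No extra test is needed, because the blood count is already taken at screening and at every later visit.
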